### Plans to promote participant retention and complete follow-up {18b}

The patients will receive extensive information about the study setup and requirements during the recruitment process. The importance of completing the follow-up will be stressed. Patients will be allowed to stop at any time during the study and will not be obliged to give a reason for discontinuation. All patients will be reminded throughout the study to fill out the questionnaires during the study visits. Throughout the follow-up period, the researchers will check responses and, if necessary, will contact the patients for completion of their follow-up.

### Data management {19}

An eCRF meeting GCP criteria will be used to collect patient data. The data entered through the REDCap system will be stored in the research folder on the protected research server and will be backed up regularly (once every 3 months). The research data (including informed consent) will be filled in, reviewed, and signed by the supervisor and the person in charge of each unit according to the data management requirements of this protocol. After the agency office is sealed, the original copy together with the original medical records will be submitted to the experimental unit for retention, one to the data management and statistical analysis unit, and one to the Shuguang Hospital affiliated with Shanghai University of Traditional Chinese Medicine. The researcher will keep all the research data, including the confirmation of all the participants (and can effectively check different records, such as the original records of the hospital), all the original informed consent forms signed by the patients, all the research medical records, and detailed records of drug distribution (Fig. 4). Shuguang Hospital affiliated with Shanghai University of Traditional Chinese Medicine will retain the clinical trial data for 5 years after the termination of the clinical trial.

### Confidentiality {27}

Research data will be stored using each participant’s research identification code. The key to the identification code list will be available only to the research team during the study and will be recorded and protected according to the research guidelines after the study is completed. Details of the patients’ identities will not be reported in the publication.

### Plans for collection, laboratory evaluation, and storage of biological specimens for genetic or molecular analysis in this trial/future use {33}

The biopsy samples will be kept in the Pathology Department of the hospital. Blood samples will be kept in the hospital laboratory. All samples will be preserved and destroyed according to the relevant hospital regulations.

## Statistical methods

### Statistical methods for primary and secondary outcomes {20a}

Full analysis set (FAS): this refers to the ideal subject set that is as close as possible to the principle of intention to analyze (including all subjects who are randomized into the group and receive at least one treatment). For the estimation of missing values of major variables, if the case data of all treatment processes cannot be observed, they will be carried forward to the missing data of the test, ensuring that the number of subjects evaluated for efficacy at the end is consistent with that at the beginning of the trial.

Per protocol set (PPS): the main variables are able to be determined for all patients who meet the experimental treatment protocol, have good compliance, use 80–120% of the experimental drugs, and complete the CRF requirements, with no missing baseline variables and no major violation of the experimental protocol.

Safety analysis set (SS): all subjects who received at least one treatment after randomization.

The main variables and comprehensive efficacy analysis constitute the full analysis set and the per-protocol set; demographic and other baseline characteristics will be analyzed using the full analysis set; the safety set will be selected for safety evaluation.

Baseline equilibrium analysis will be conducted in FAS.

The equilibrium analysis of the basic value is aimed at the basic demographic characteristics, vital signs, and curative effect-related indicators, among others, on enrollment into the group, to explain whether the basic characteristics of the two groups are comparable. Among them, the quantitative indicators (such as age, course of disease, temperature, pulse, respiration, systolic blood pressure, diastolic blood pressure, and TCM syndrome score) of the two groups will be listed, including the number of cases, means, standard deviations, medians, maxima, and minima. The two groups will be compared by ANOVA and the Kruskal-Wallis rank sum test. The frequencies and percentages of qualitative indicators (such as nationality, marital status, heart rate, history, allergy history, single symptom) will be listed and compared by *χ*^2^ test/precise probability method/rank sum test.

Analysis of efficacy will be carried out in both FAS and PPS. According to the OLGA/OLGIM staging changes after treatment, the efficacy of CAG will be divided into progressive, stable, and improved. The numbers and percentages of cases will be calculated according to the efficacy rate. The CMH chi-square test stratified by center will be used to compare the two groups, and the 95% confidence interval of the rate difference between the two groups will be calculated. The curative effect on clinical symptoms will be calculated by the number and percentage of cases classified as cured, markedly effective, effective, and ineffective. The CMH chi-square test stratified by center will be used to compare the two groups. For the assessment of the changes in mucosal histology before and after treatment, changes after treatment will be evaluated relative to the baseline, and the number of cases, means, standard deviations, medians, maxima, and minima will be calculated and compared within the groups using paired *t*-test/signed-rank tests and compared between the two groups by analysis of variance. A covariance analysis model will be used to compare the difference between the two groups after treatment relative to the baseline. In the model, the baseline will be taken as the covariate, and the effects of grouping and center will be considered. The least-squares mean and 95% confidence interval of the difference between the groups are calculated based on this model.

The safety analysis will be carried out in SS. Adverse events will be recorded according to their occurrence and the numbers and percentages of cases will be listed and compared using the chi-square test/Fisher exact probability method. During the treatment, all adverse events will be classified and coded according to the common term evaluation standard for adverse events (CTCAE 4.0). The number of cases, times, and incidence rates will be calculated according to the system organ classification and standard name after coding, and the details will be described in a list. Laboratory examinations related to safety: all completed laboratory examination items will be listed in the form of a cross table before and after treatment (according to their clinical significance), and abnormal results obtained after treatment will be listed. Vital signs: changes in physical signs (body temperature, heart rhythm, respiration, systolic blood pressure, diastolic blood pressure) before and after treatment will be described and the number of cases, means, standard deviations, medians, maxima, and minima will be calculated and compared using ANOVA, with the abnormal results listed after treatment.

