#### Inclusion criteria

Patients must meet the following criteria to be eligible for enrollment:Patients aged 18–70 years, male or femalePatients who meet the diagnostic criteria of chronic atrophic gastritis and who test negative for *Helicobacter pylori* (13C or 14C urea breath test is required)Patients with a pathological stage of OLGA-II/III. Two experts from the Department of Pathology will perform the diagnosis (pathological film reading), with consensus on the pathological conclusionPatients who have voluntarily agreed to participate and who have signed informed consent

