### Sample size {14}

The design is a randomized, double-blind, double-dummy, parallel-controlled, multicenter clinical trial. The sample ratio of the treatment group and the control group is 1:1. Based on the preliminary results of clinical research [8, 9], the expected efficacy of Elian Granules on chronic atrophic gastritis is 85%, with 63.3% of the therapeutic effect of Weifuchun used as the placebo effect. According to relevant references [16, 17] and the above data, two independent proportions superiority power analysis is used to estimate the sample size based on *α* = 0.05, *β* = 0.10, and power = 0.90 by Pass 11.0. It was estimated that no fewer than 95 subjects should be enrolled in each group. Allowing for a 20% drop-out, we, therefore, propose the recruitment of a total sample size of 220 patients. Referring to the phase II clinical trial, the planned total sample size is 240 cases in two groups. In terms of competition, each center should provide no fewer than 20 cases.

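### The centre-stratified comparison of the improved/stable/progressive classes leaves out baseline OLGA stage, a modest and avoidable loss of efficiency

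*Protocol article*

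**What the plan says.** Under Inclusion criteria, entry is limited by baseline stage: "Patients with a pathological stage of OLGA-II/III". The primary outcome section then compares each patient's stage after 24 weeks with his or her own stage before treatment: a fall is improvement, no change is stability, a rise is progression.

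The statistical methods section ({20a}) compares the arms on these classes as follows: "The CMH chi-square test stratified by center will be used to compare the two groups, and the 95% confidence interval of the rate difference". Centre is the only stratifying factor named. The section does not say which CMH statistic is meant, or which classes make up the efficacy rate.

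For changes in mucosal histology the same section plans within-group tests, an analysis of variance between groups, and a covariance model: "In the model, the baseline will be taken as the covariate, and the effects of grouping and center will be considered". It does not say which of these analyses decides the trial.

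The sequence generation section describes central randomisation in blocks of 4 and names no stratum for stage. The sample size section treats the outcome as binary: "two independent proportions superiority power analysis is used to estimate the sample size".

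**The concern.** A class defined as change from baseline is not thereby adjusted for baseline, because change usually remains correlated with its starting value. If stage III patients are more or less likely than stage II patients to be classed as improved, two things follow. A chance difference between arms in the share at stage III shifts the observed rate difference, and the variation explained by stage stays in the error of the comparison.

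The plan accepts this argument for mean change, where baseline enters the covariance model, but does not carry it to the categorical comparison that matches the primary outcome. At stake is some power, and a treatment estimate that can be questioned if the arms happen to differ in stage.

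**Working it through.** **1. The plan's own figure.** Inputs from the sample size section: p1 = 0.85, p2 = 0.633, α = 0.05 (taken as two-sided), power 0.90, ratio 1:1. With p̄ = 0.7415 and d = 0.217:

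n = [1.960·√(2·0.7415·0.2585) + 1.282·√(0.85·0.15 + 0.633·0.367)]² / 0.217² = (1.2135 + 0.7687)² / 0.04709 = 83.4, so 84 per group.

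With continuity correction: (83.4/4)·[1 + √(1 + 4/(83.4·0.217))]² = 92.4, so 93 per group. The stated 95 is reproduced to within 2 patients. Power without correction is 93.4% at 95 per group and 97.4% at 120 per group.

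**2. The planned effect as an odds ratio.** (0.85/0.15)/(0.633/0.367) = 5.67/1.72 = 3.3. This is a large effect, so there is little power left to gain.

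**3. Size of chance imbalance.** Assume 40% at stage III (not in the documents) and 120 per arm. The SD of the between-arm difference in that share is √(2·0.4·0.6/120) = 0.063, or 6.3 points. If improvement differed by 35 points between stages (assumed 25% versus 60%), one SD of imbalance moves the rate difference by 0.35 × 6.3 = 2.2 points. For scale, the planned difference is 21.7 points, and its standard error at the planned rates is √[(0.1275 + 0.2323)/120] = 5.5 points.

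**4. Power with and without stage, placebo rate 63.3%.** Simulation with 3000 trials per row, 10 equal centres, two-sided 5% and a linear score model on the ordered classes. Assumptions: improved is the planned rate, 10% progression on control, 40% at stage III, proportional odds. The stage odds ratio is varied because the documents do not give it.

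| Rates | Evaluable | Stage odds ratio | Centre only | Centre + stage |
|---|---|---|---|---|
| 85 vs 63.3% | 190 | 1 | 91.8% | 91.5% |
| | 190 | 2 | 91.8% | 92.1% |
| | 190 | 4 | 93.5% | 95.1% |
| | 240 | 1 | 96.7% | 96.6% |
| | 240 | 2 | 97.1% | 97.0% |
| | 240 | 4 | 97.0% | 97.8% |
| 78 vs 63.3% | 190 | 1 | 57.8% | 57.5% |
| | 190 | 4 | 60.5% | 63.8% |
| | 240 | 1 | 70.6% | 70.1% |
| | 240 | 4 | 69.3% | 71.5% |

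The rows with stage odds ratio 1 differ only by simulation noise. Type I error was 5.1% to 5.4% for both models.

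**5. Smaller effect with a lower placebo rate.** Assume a treatment odds ratio of 2.1, 240 patients, and placebo improvement of 25% (II) and 60% (III). The average is 0.6·25 + 0.4·60 = 39%, and the stage odds ratio is (0.60/0.40)/(0.25/0.75) = 4.5. Ordered analysis by centre only gives 77%, with stage added 82%. With equal progression in both stages the figures are 75% and 79%. With no prognostic effect both are 84%. A further run put the gain at about 4 to 6 points.

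**6. Form of adjustment.** Crossing stage with centre gives 10 × 2 = 20 strata, on average 240/20 = 12 patients each. In simulation this full stratification could lose 1 to 3 points. Stage added to centre as a covariate did not lose power.

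**7. Ordering, if three classes are tested.** At 85 versus 63.3% and 190 evaluable, a 2-df general-association CMH has 87 to 89% power and the 1-df row-mean-score CMH 92 to 94%. At 78 versus 63.3% the gap is 8 to 10 points. A binary CMH on improved has 93 to 94% at 190, so on that reading nothing is lost.

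**The case against.** The strongest case against is that a centre-stratified CMH is a standard and valid test, that baseline is partly handled, and that the rest is preference. The classes are relative to each patient's own stage, a baseline-adjusted covariance model is planned, and baseline balance will be checked. Patients at stage II and at stage III can each move at least one stage in either direction, so greater room to fall at stage III does not by itself make stage prognostic. At the protocol's rates the gain is close to nothing. All of this stands, and it limits the point to efficiency. It does not remove it: the protocol itself chose the stratifier, the covariance model does not adjust the rate difference, and the covariate is already collected.

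A reader might also infer that the plan ignores the ordering of the classes. The text does not support that. It names no CMH statistic, and the CMH family includes an ordinal one. The efficacy rate, the rate difference and the two-proportion sizing all fit a binary test with 1 degree of freedom, where there is no ordering to lose. The signed rate difference with its interval also keeps the direction of effect.

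A reader might likewise infer a gain of some 20 points. That requires combining the 2-df reading with placebo improvement of 20% versus 70% by stage, a stage odds ratio of (0.70/0.30)/(0.20/0.80) = 9.3. No section supports either.

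**Conclusion.** The point holds as a matter of efficiency and protection against chance imbalance, not of validity or bias. The comparison that matches the primary outcome omits a baseline variable from which that outcome is computed, while the same section uses baseline elsewhere.

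The size is small under the plan's own assumptions: about 0 to 2 points of power at 85% versus 63.3%. It is larger only if two things hold together, a smaller effect and a strongly prognostic stage. It is then 2 to 3 points at a placebo rate of 63.3% and a stage odds ratio of 4, and about 4 to 6 points at a placebo rate near 39% and a stage odds ratio of 4.5. The smaller effect deserves attention because the placebo rate is borrowed from another treatment ("63.3% of the therapeutic effect of Weifuchun used as the placebo effect"). The stage III share, the stage odds ratios and the smaller effects are assumptions. If stage is not prognostic, the adjustment costs nothing measurable.

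**What to change.** Before unblinding, amend the statistical methods section as follows.

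- State which analysis decides the trial and which classes form the efficacy rate.
- In that analysis, include arm, centre and baseline OLGA stage (II or III), with stage as an additive covariate. Do not cross stage with the 10 centres as CMH strata.
- Report the rate difference and its 95% CI standardised over centre and stage.
- Keep the centre-stratified CMH as sensitivity analysis.
- If the three classes rather than a binary rate are tested, name an ordered 1-df analysis: an ordinal model with the same covariates or, without covariates, CMH row mean scores. Do not use the 2-df general-association statistic.

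The simulations above used a linear score model. If a proportional-odds model is chosen, its behaviour with 10 centres and sparse classes should be checked before it is fixed.

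The cost is wording and programming only. Stage comes from the screening biopsy, so no visit, procedure or patient is added.

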##### Dyspepsia symptoms

A symptom score system will be used to evaluate the improvement in dyspepsia (Table 3). In the symptom score system, the score will be determined according to the severity, duration, and frequency of symptoms. The symptom scores will be recorded before administration and after 4 weeks, 12 weeks, and 24 weeks. The overall score represents the sum of all symptom scores. The dyspepsia symptom scores and the changes in each index value before and after treatment will be compared between groups. The treatment effect index (TEI) will be calculated as (pre-treatment integral − post-treatment integral)/pre-treatment integral × 100%. The curative effect classification is as follows: TEI ≥ 90% indicates clinically cured; 90% > TEI ≥ 70% indicates marked efficacy; 70% > TEI ≥ 30% indicates efficacy; TEI < 30% indicates invalid.

**Table 3 Tab3:** The symptom score system for chronic atrophic gastritis

Symptom	Score	Degree	Grading system
Epigastric pain	1	None	-
	2	Mild	< 2 times a week
	3	Moderate	≥ 3 times a week, not every day
	4	Severe	Every day, intermittently
	5	Extreme severe	Every day, almost continuously
Epigastric distention	1	None	-
	2	Mild	< 2 times a week
	3	Moderate	≥ 3 times a week, not every day
	4	Severe	Every day, intermittently
	5	Extreme severe	Every day, almost continuously
Epigastric discomfort	1	None	-
	2	Mild	< 2 times a week
	3	Moderate	≥ 3 times a week, not every day
	4	Severe	Every day, intermittently
	5	Extreme severe	Every day, almost continuously
Early satiety	1	None	-
	2	Mild	< 2 times a week
	3	Moderate	≥ 3 times a week, not every day
	4	Severe	Every day, intermittently
	5	Extreme severe	Every day, almost continuously
Heartburn	1	None	-
	2	Mild	< 2 times a week
	3	Moderate	≥ 3 times a week, not every day
	4	Severe	Every day, intermittently
	5	Extreme severe	Every day, almost continuously
Acid regurgitation	1	None	-
	2	Mild	< 2 times a week
	3	Moderate	≥ 3 times a week, not every day
	4	Severe	Every day, intermittently
	5	Extreme severe	Every day, almost continuously
Belching	1	None	-
	2	Mild	< 2 times a week
	3	Moderate	≥ 3 times a week, not every day
	4	Severe	Every day, intermittently
	5	Extreme severe	Every day, almost continuously
Abdominal discomfort	1	None	-
	2	Mild	< 2 times a week
	3	Moderate	≥ 3 times a week, not every day
	4	Severe	Every day, intermittently
	5	Extreme severe	Every day, almost continuously
Total symptom score	Equal to the sum of the above scores		

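### The one test named for symptoms compares coarse percent-change classes without baseline adjustment, and the covariance model already in the plan is not clearly assigned to the dyspepsia score

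*Protocol article*

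**What the plan says.** The Dyspepsia symptoms subsection of Outcomes {12} sums eight symptoms, each scored 1 to 5 (Table 3), at baseline and weeks 4, 12 and 24. It then does two things with the total. First, "The dyspepsia symptom scores and the changes in each index value before and after treatment will be compared between groups"; no method is given. Second, it defines the treatment effect index (TEI), the fall as a percentage of the baseline total, and cuts it at 30%, 70% and 90% into four classes.

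The statistical methods section {20a} takes up the second: "The curative effect on clinical symptoms will be calculated by the number and percentage of cases classified as cured, markedly effective, effective, and ineffective". The classes are compared by a CMH chi-square stratified by centre. No effect estimate or confidence interval is named for symptoms; the interval mentioned just before belongs to the OLGA/OLGIM rate difference.

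The same paragraph later describes a covariance model: "In the model, the baseline will be taken as the covariate, and the effects of grouping and center will be considered". It yields a least-squares mean difference with a 95% interval. It comes directly after the sentence on changes in mucosal histology, and its outcome is not named.

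**The concern.** Cutting a 33-point total into percent-change classes throws away information, and a test stratified only by centre leaves the baseline score unused. Take a baseline total of 20. A fall to 14 (6/20 = 30%) and a fall to 8, meaning no symptoms at all (12/20 = 60%), land in the same class. A fall to 15 (25%) and a rise to 24 (−20%) both count as invalid. A single point, 14 against 15, changes the class.

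Dyspepsia is one of the two secondary outcomes named in the abstract, and the trial is meant to inform a phase III study. If the class test is what gets reported, a modest symptom benefit could go undetected, and there would be no mean difference with an interval to carry forward.

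**Working it through.** **1. The plan's own figure.** The protocol states no power for symptoms. Its only sizing is on a response rate: "the expected efficacy of Elian Granules on chronic atrophic gastritis is 85%, with 63.3% of the therapeutic effect of Weifuchun used as the placebo effect", with α = 0.05 and power 0.90. Two-sided, without continuity correction:

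n = [1.960·√(2·0.7415·0.2585) + 1.282·√(0.85·0.15 + 0.633·0.367)]² / 0.217² = 83.4, so 84 per group.

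With the continuity correction it is 93, close to the stated 95. This only sets the scale of the trial: "the planned total sample size is 240 cases in two groups", or 120 per arm, and 96 per arm after the 20% drop-out allowance (240 × 0.8 = 192).

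**2. What the classes can hold.** The total runs from 8 × 1 = 8 to 8 × 5 = 40. For baseline total B the largest possible TEI is (B − 8)/B.

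| Class | TEI needed | Smallest B that can reach it |
|---|---|---|
| Clinically cured | 90% | none: at B = 40 the maximum is 32/40 = 80% |
| Marked efficacy | 70% | 27 (19/27 = 70.4%; 18/26 = 69.2%) |
| Efficacy | 30% | 12 (4/12 = 33.3%; 3/11 = 27.3%) |

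The maximum is 50% at B = 16 and 60% at B = 20. The inclusion criteria set no minimum symptom score. So one class is empty by construction and a second is open only to patients with high baselines.

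**3. Power, by simulation.** Week-24 and baseline totals were simulated in 10 centres. The class test (CMH by centre) was compared with ANCOVA on the week-24 total (baseline, group, centre) at two-sided 0.05. All symptom parameters are assumptions, because the protocol gives none.

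| Setting | Class test against ANCOVA |
|---|---|
| 120 per arm; baseline mean 16–26, SD 3–5; correlation 0.3–0.7; effect 0.35–0.40 SD | general-association CMH 0.42–0.92, ANCOVA 0.73–0.997; loss about 8–38 points (mean-score CMH about 8–37) |
| Same, 100 per arm | loss about 11–39 points |
| 96 per arm, effect 0.35 SD, mean-score CMH | loss about 18–39 points |
| Proportional-improvement model | loss 11–39 (general) or 10–33 (mean-score) points |
| 96 per arm; items rescored 0–4 (floor removed); baseline mean 16 or 20, SD 4 or 5; effect set so that ANCOVA has 72–78% power | loss 8–20 (mean-score) or 25–35 (general) points |

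Type I error was about 4–5% for every test, so the gap is one of efficiency.

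**4. Dependence on the effect.** At 120 per arm and correlation 0.5 the loss was about 14–17 points at 0.2 SD, 24–29 at 0.3 SD, 9–14 at 0.5 SD, 3–5 at 0.6 SD and 0 at 0.8 SD. It shrinks at the top because both tests approach full power.

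**5. How many classes are in use.** With baseline 20 (SD 5), a control fall of 6 points and an effect of 0.3 SD, the shares were 44.6% invalid, 55.2% efficacy, 0.2% marked and 0% cured. With baseline 16 (SD 3), a control fall of 3 points and the same effect, the general CMH, the mean-score CMH and a plain 30% split all had power 0.471, against 0.733 for ANCOVA. As scored, the four-class test is in effect a responder test at 30%.

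**The case against.** The strongest reply is that the score is not discarded. Outcomes {12} plans a between-group comparison of the scores and their changes before it defines TEI, and nothing makes the class test the deciding one. A reader might infer that the trial will analyse symptoms only as classes; the documents do not support that. Nor do they show that the covariance model excludes symptoms. It names no outcome, least-squares means suit a quantitative score, and SF-12 has no other method either, which favours a generic reading. The method for the score comparison could properly sit in an analysis plan that is not shown. All of this stands, and it limits the point to an unclear assignment plus an inefficient named test.

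A reader might also take the power loss as a fixed property of the trial. It is not: it rests on assumed SDs, correlations and a modest effect. The figures for the scale as scored also include the floor of 8, which is a fault separate from categorising; the rescored runs show what remains without it. Nor should the 70% cut be blamed: with mean baselines of 16–20, few patients could come near it.

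Finally, this is a secondary outcome for which no power is claimed, and the primary sizing is untouched. What the reply does not remove is that the protocol itself chooses a symptom test, that this test is the weaker one, and that even on the generous reading two symptom analyses stand side by side with no statement of which is the main one.

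**Conclusion.** The point holds in limited form. The only test {20a} names specifically for symptoms is a centre-stratified CMH on TEI classes. That test ignores baseline, has an unreachable top class, and behaves nearly as a 30% responder split. The better model is in the plan but not clearly assigned to this score.

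For an effect of about 0.35–0.40 SD with 96–120 per arm, baseline mean 16–20, SD 4–5 and correlation 0.3–0.7, the loss is roughly 10–40 points of power as scored. Without the scale floor it is about 8–20 points for an ordered CMH; the plan does not say which CMH form is meant, and general association loses more. The loss is small for effects well above this range and nil at about 0.8 SD. These inputs are assumptions, so the size is conditional; the unreachable class follows from Table 3 alone. The change is worth making for a named secondary outcome, and the primary analysis is not affected.

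**What to change.** In the statistical methods section {20a}, state that the main symptom analysis is the covariance model already described, applied to the week-24 total dyspepsia score: baseline total as covariate, group and centre as factors, least-squares mean difference with 95% confidence interval. Say that this is the between-group score comparison promised in Outcomes {12}. Report the TEI classes as numbers and percentages by group, as description. Make the change before database lock and unblinding.

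The cost is wording only: no new data, visits or patients. The small downside is that the familiar effective rate is no longer the tested symptom result, though it stays in the report.

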### Safety outcomes

The following tests will be performed on all subjects during the study: physical examination (temperature, respiration, heart rate, blood pressure, height, and weight); gastroscope and biopsy; complete blood cell count; urinalysis; liver function (ALT, AST, alkaline phosphatase [ALP], serum total bilirubin [TBIL], and γ-glutamyl transpeptidase (γ-GT)); renal function (Cr, BUN) and glomerular filtration rate (GFR); and electrocardiography (ECG). In addition, a urine pregnancy test will be carried out for female patients of childbearing age.

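### Vital-sign changes are to be compared by ANOVA without the baseline-adjusted model the protocol already specifies for efficacy, and heart rhythm stands among the numeric signs where heart rate appears to be meant (minor)

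*Protocol article*

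**What the plan says.** The safety paragraph of Statistical methods for primary and secondary outcomes {20a} states that "changes in physical signs (body temperature, heart rhythm, respiration, systolic blood pressure, diastolic blood pressure) before and after treatment will be described", and then that "means, standard deviations, medians, maxima, and minima will be calculated and compared using ANOVA, with the abnormal results listed after treatment". It names neither a covariate nor the groups being compared.

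Three other places bear on this:

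- Safety outcomes gives the measurements as "physical examination (temperature, respiration, heart rate, blood pressure, height, and weight". Heart rate is there. Rhythm is not part of the physical examination, although an ECG is done.
- The baseline paragraph of {20a} has among its quantitative indicators "temperature, pulse, respiration, systolic blood pressure, diastolic blood pressure, and TCM syndrome score", but also lists "qualitative indicators (such as nationality, marital status, heart rate, history, allergy history, single symptom".
- The efficacy paragraph of {20a} describes a covariance analysis of change: "In the model, the baseline will be taken as the covariate, and the effects of grouping and center will be considered". It yields a least-squares mean difference with a 95% confidence interval.

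Table 5 (Participant timeline {13}) schedules the physical examination at Visit 1 and again at Visits 3, 4 and 5.

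**The concern.** There are two separate matters in one sentence.

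First, the article names a method for vital signs, so this is a stated choice and not a detail left open. The method named is the less precise of two that the same section describes, and the data for the better one are already collected.

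Second, the list of signs cannot be carried out as worded. A rhythm is a category and has no useful mean, standard deviation or ANOVA. A programmer who followed the sentence literally would have no heart-rate change to summarise. One who followed the baseline paragraph literally would summarise pulse as a number and heart rate as frequencies.

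At stake are the precision of some supporting safety comparisons and the clarity of one variable. No efficacy result, sample size or error rate in the protocol depends on either.

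**Working it through.** **Which comparison is meant.** The vital-sign sentence does not say. The efficacy paragraph, describing changes in histology, uses paired t or signed-rank tests within groups and analysis of variance between the two groups. By that parallel, ANOVA in the safety paragraph is most naturally the comparison of the two arms.

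**Precision.** The protocol states no figure for this analysis, so there is nothing to reproduce first.

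Inputs:
- 240 patients at 1:1, so 120 per arm (Sample size {14}).
- Correlation r between baseline and follow-up: not in the document, assumed 0.3 to 0.9.
- SD s: not in the document, taken as equal at both times, with results in units of s.

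Formulas:
- ANOVA on change: variance per patient = 2(1 − r)s².
- Covariance model: variance per patient = (1 − r²)s² = (1 − r)(1 + r)s².
- Ratio, covariance model to change score = (1 + r)/2. The ratio of standard errors is its square root.
- Detectable difference at 80% power, two-sided 5%, with v the variance per patient in units of s² = (1.960 + 0.842) × √(2v/120).

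Worked for r = 0.5: the variances are 1.00 and 0.75, the ratio is 0.75 and √0.75 = 0.866, so the standard error is 13% smaller. The detectable difference is 2.802 × √(2/120) = 0.362 for change and 2.802 × √(1.5/120) = 0.313 for the covariance model.

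| r | 2(1 − r) | 1 − r² | Variance ratio | SE ratio | SE smaller by | Detectable, change (SD) | Detectable, covariance model (SD) |
|---|---|---|---|---|---|---|---|
| 0.3 | 1.40 | 0.91 | 0.65 | 0.806 | 19% | 0.428 | 0.345 |
| 0.5 | 1.00 | 0.75 | 0.75 | 0.866 | 13% | 0.362 | 0.313 |
| 0.7 | 0.60 | 0.51 | 0.85 | 0.922 | 8% | 0.280 | 0.258 |
| 0.9 | 0.20 | 0.19 | 0.95 | 0.975 | 2.5% | 0.162 | 0.158 |

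The percentages do not depend on the number of patients. The detectable differences take all 120 per arm and no drop-out. Both are large-sample figures and leave out any further gain or small cost from the centre terms.

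**Rate and rhythm, side by side.**

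| Place | Treated as a number | Treated as a category |
|---|---|---|
| Safety outcomes | heart rate (measured) | – |
| {20a}, baseline | pulse | heart rate |
| {20a}, safety | heart rhythm | – |

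If heart rate and heart rhythm change places in the two {20a} paragraphs, each list makes sense: pulse as a number and rhythm as a category at baseline, and rate as a number in the safety analysis. That pattern points to swapped terms and not to a decision to leave heart rate out.

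**The case against.** The best defence is that nothing here is invalid. A change score already uses baseline. In a 1:1 randomized trial, ANOVA on change is unbiased and keeps its type I error, and the efficacy paragraph itself uses analysis of variance on change before adding the covariance model. Objectives {7} ties the safety endpoint to the number of treatment-related adverse events, which are compared by chi-square or Fisher test. Vital signs are supporting data, and power to detect a shift in them is not a design requirement. All of this stands. It limits the first matter to efficiency and makes the whole point minor. It does not remove the inconsistency over rate and rhythm.

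Three stronger readings are tempting, and the document does not support them.

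- A reader might infer that exactly one sign, heart rate, is dropped from the safety analysis. The listing of pulse as quantitative makes a slip of terms more likely. The count would also be wrong, since weight is measured too and is absent from the vital-sign list.
- A reader might infer that the laboratory values need the same model, because they are only "listed in the form of a cross table before and after treatment (according to their clinical significance" and abnormal results are then listed. That is a legitimate safety summary. A continuous between-arm model would be an extra analysis, and a power contrast with a test of proportions would be set against a test that the protocol does not plan.
- A reader might take the between-arm comparison as stated. It is an inference by parallel, although a natural one.

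**Conclusion.** The point holds as a minor one, in two parts.

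1. The terms for heart rate, pulse and heart rhythm are inconsistent across Safety outcomes and two paragraphs of {20a}, and the vital-sign sentence cannot sensibly be applied to rhythm. This is a correction of wording.
2. The named ANOVA gives up precision that the covariance model in the same section would recover without new data: about 19% of the standard error at r = 0.3, falling to 2.5% at r = 0.9. This is an improvement and not the repair of an error.

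The size rests on equal variances at the two times and on assumed correlations. The direction does not: in large samples, estimating the baseline slope does no worse than fixing it at one, which is what a change score does. For a sign that is strongly correlated over time the gain is negligible.

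**What to change.** In the safety paragraph of {20a}, replace ANOVA for the continuous vital signs by the model already in the efficacy paragraph: post-treatment value on arm, with baseline as covariate and centre as a factor. Report the adjusted difference between arms with its 95% confidence interval, say that the comparison is between arms, and state that it is read descriptively. Keep the summary statistics and the listing of abnormal results.

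In the same paragraph, name heart rate (pulse) in place of heart rhythm. In the baseline paragraph, take heart rate out of the qualitative list, so that heart rate (pulse) stands once, among the quantitative signs. If rhythm is wanted, take it from the ECG and tabulate it as normal or abnormal.

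The cost is a few words in the protocol or analysis plan and a few lines of code. No new data are needed, and no sample size or error rate changes.
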